### Aim 2: explore implementation outcomes, including acceptability, adoption, appropriateness, feasibility, fidelity, penetration, sustainability, and cost across training conditions

#### Analyses

Using the taxonomy of implementation outcomes defined by Proctor et al. [87], data will be collected on acceptability, adoption, appropriateness, feasibility, fidelity, penetration, and sustainability. We have four main hypotheses related to implementation outcomes. First, we hypothesize that rates of acceptability and appropriateness of PCIT will be high and equal across groups. Without doing a formal hypothesis test, we will examine the rates of acceptability and appropriateness. Second, we hypothesize that rates of adoption, fidelity, and feasibility will be the highest among the more active training conditions (LC, CM). As in Aim 1, we will compare these measures using a one-way ANOVA, with Bartholomew’s test for the ordered alternative. Third, we hypothesize that implementation costs will be lowest for the DE and highest for LC. We will compare the costs per clinician for the various treatments using ANOVA comparing the three once again. Measurement and analysis of cost will be supported by a consulting health economist. Finally, we hypothesize that participants in the LC will evidence greater penetration and sustainability of PCIT within the service settings. Because penetration is a proportion, we will first stabilize variances using the arcsin transform; we will then use one-way ANOVA as in Aim 1.

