### Outcome measures and assessment procedures

The three primary outcomes of interest are training, implementation, and client outcomes. A review of outcomes measures across participants and timepoints is provided in Table 2.

**Table 2 Tab2:** Assessment measures across timepoints and participants

Construct	Measure	Brief description	Timepoints	Participant(s)	Method
Training outputs					
Knowledge					
	The PCIT Coaches Quiz [96]	22-items to assess clinicians’ knowledge of PCIT concepts and coaching scenarios; mixed question format of multiple choice and short answer	Baseline	Supervisors	Self-report
			12 months	Clinicians	
			24 months		
Skill					
	PCIT Therapist Competency Checklist	17-item checklist of PCIT competency criteria based on established PCIT Training Guidelines	Ongoing	Completed by the trainer on clinicians	Live Behavior observation
	FIRST Coach Coding System [97]	Assesses the quality and style of a therapist’s coaching	Ongoing	Completed by the trainer on clinicians	Video review behavior observation
	Supervisor Impressions of Competence in PCIT [98]	Supervision structure, practice, content, and skill	6 months	Completed by the supervisors on clinicians	Supervisor Report of clinician behavior
			12 months		
			24 months		
Attitude					
	Training Satisfaction [99]	Satisfaction with on-site training materials, content, and trainer	During each on-site training	Supervisors	Self-report
				clinicians	
	Treatment Satisfaction	Satisfaction with the treatment, concerns or barriers to using PCIT, and suggestion for improving its relevance	6 months	Supervisors	Self-report
			12 months	Clinicians	
			24 months		
	Usage Rating Profile—Intervention [100]	35-item measure of intervention usage, including acceptability, understanding, feasibility, and system support	6 months	Supervisors	Self-report
			12 months	Clinicians	
			24 months		
	PCIT Learning Experience Feedback Form	8-item survey to assess satisfaction with PCIT training	6 months	Administrators	Self-report
			12 months		
			24 months		
Training inputs					
Trainee characteristics					
	Demographic Information Form	Basic demographic and contact information	Baseline	Administrators	Self-report
				Supervisors Clinicians	
	Treatment Provider and Practices Survey [101]	Demographic information and variables hypothesized to affect adoption of EBTs	Baseline	Supervisors Clinicians	Self-report
Training design					

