### Trial status

To date, all four waves of training have been initiated. Training efforts and clinical consultation will continue through 2016. County and clinic recruitment is now complete, with 50 clinics, representing 37 randomization units enrolled in the study, which is lower than the originally predicted enrollment of 72 clinics [91]. From participating agencies, 100 clinicians, 50 supervisors, and 50 administrators have been enrolled. Additionally, 26 “second generation” clinicians have been enrolled and will continue to be enrolled as the study progresses. At the time of the manuscript acceptance (9/16/15), 203 families had consented to participate in the study; 198 families had completed the baseline assessment. Family enrollment is expected to continue through December 31, 2016, and it is anticipated that family enrollment will surpass the target of 288. Thus far, retention rates have varied across participant types but have remained high. As indicated above, we anticipate a 96 % retention rate for professional participants; to date, 94 % of professionals have been retained. We anticipate an 88 % retention rate for families; to date, 95 % of families have been retained. Likewise, data collection thus far has yielded assessment completion rates of 93 % for professional participants and 86 % for families. A few study team decisions have influenced these rates: (1) we kept in the study all clinicians who left their original agencies and (2) (if possible) we included families from these clinicians who were seen in new agencies. We recognize that these rates currently are within or surpass the expected range; however, it is early in the study timeline, and many things likely will affect final rates.

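### Aim 2's first main hypothesis is equality of acceptability and appropriateness across arms, but the stated method is to look at untested rates, which cannot support equality at this sample size

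*Protocol article*

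**What the plan says.** The Analyses text under Aim 2 announces: "We have four main hypotheses related to implementation outcomes". The first of them reads: "First, we hypothesize that rates of acceptability and appropriateness of PCIT will be high and equal across groups". The next sentence fixes how it will be addressed: "Without doing a formal hypothesis test, we will examine the rates of acceptability and appropriateness".

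The other three hypotheses are handled differently. For adoption, fidelity and feasibility the article says: "As in Aim 1, we will compare these measures using a one-way ANOVA, with Bartholomew’s test for the ordered alternative". Cost per clinician is compared by ANOVA, and penetration by ANOVA after an arcsine transformation. The equality hypothesis is the only one of the four without a between-arm comparison method.

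The article gives mixed signals on status. The heading is "Aim 2: explore implementation outcomes, including acceptability, adoption, appropriateness, feasibility, fidelity, penetration, sustainability, and cost across training conditions", which is exploratory wording. The outcome measures section says: "The three primary outcomes of interest are training, implementation, and client outcomes".

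Neither the Aim 2 text nor the sections on proposed analyses, nesting and missing data state an equivalence margin, a threshold for a high rate, or an interval for the between-arm difference.

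**The concern.** Equality is a claim about how large a difference can be ruled out. Observed rates alone do not answer that, because two arms can show the same rate by chance while their true rates differ. The reverse also happens: identical arms can show a visible gap. The reader can judge which is plausible only from the precision of the difference, and the stated method supplies none.

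This is a method that the article chose and put in print, so it is more than a detail left for the analysis plan. What is at stake is limited to the statement about acceptability and appropriateness itself. A later report could describe the arms as equal on evidence that is compatible with a substantial gap.

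**Working it through.** **Plan's own figure.** The article gives no sample size, power, expected rate, margin or interval for this hypothesis, so there is nothing to reproduce. The calculation below only shows how precise a comparison of rates can be.

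**Inputs from the article**
- Trial status: "From participating agencies, 100 clinicians, 50 supervisors, and 50 administrators have been enrolled", in 50 clinics representing 37 randomization units.
- Table 2: the Treatment Implementation Feedback Form, listed under treatment process and acceptability, is completed by supervisors and clinicians. That gives 100 + 50 = 150 respondents, or 150/50 = 3 per clinic.

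**Assumptions not in the article**
- Equal arms, so n = 150/3 = 50 per arm.
- A common rate of p = 0.85.
- Clinic intraclass correlation (ICC) of 0, 0.1 or 0.2.
- Complete response at a single timepoint.

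**Formulas**
- Design effect DE = 1 + (3 − 1) × ICC, which gives 1.0, 1.2 and 1.4.
- 95% half-width for a pairwise difference in rates = 1.96 × √(2 × p(1 − p) × DE / n).
- The same in SD units for a scale score = 1.96 × √(2 × DE / n).

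**Results**

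| ICC | DE | Half-width, rates | Half-width, SD |
|---|---|---|---|
| 0 | 1.0 | 1.96 × √(0.255 × 1.0/50) = 14.0 points | 1.96 × √(2.0/50) = 0.39 |
| 0.1 | 1.2 | 1.96 × √(0.255 × 1.2/50) = 15.3 points | 1.96 × √(2.4/50) = 0.43 |
| 0.2 | 1.4 | 1.96 × √(0.255 × 1.4/50) = 16.6 points | 1.96 × √(2.8/50) = 0.46 |

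**Cross-check with other inputs.** Clustering on the 37 randomization units gives 150/37 = 4.05 respondents per unit. With p of 0.80 or 0.90 and ICC from 0 to 0.10:
- 50 per arm: half-width about 12 to 18 points.
- Clinicians only (about 33 per arm): about 14 to 21 points.
- The 253 families expected to complete all assessments (about 84 per arm): about 9 to 15 points.

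**How often similar rates mislead.** Under the same cross-check assumptions with 50 per arm, a true 15-point gap between two arms would appear as less than 10 points in about 25 to 30% of trials.

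**Could equality be shown if it were true?** All three pairwise 95% intervals lie inside a margin M only if the largest observed difference is below M minus the half-width. Take M = 0.5 SD and three truly identical arms:

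| ICC | Largest observed difference allowed | Chance that all three intervals fit |
|---|---|---|
| 0 | 0.5 − 0.39 = 0.11 SD | about 15% |
| 0.1 | 0.5 − 0.43 = 0.07 SD | about 6% |
| 0.2 | 0.5 − 0.46 = 0.04 SD | about 1% |

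On the rate scale, a 10-point margin is out of reach because every half-width in the first table exceeds 10 points. A 15-point margin leaves 1 point of slack at ICC 0 and none at 0.1 or 0.2. At 20 points, the power to show equivalence for a single pair (two one-sided 5% tests, cross-check assumptions, no true difference) is 41 to 91%. Fitting all three pairs at once is harder.

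**The case against.** The best defence is that the article is open about what it does. Aim 2 is framed as exploratory, this item is expressly limited to description, and no sentence says that equality will be declared. Declining to test also avoids a worse practice, which is reading a non-significant result as proof of no difference. Margins and intervals are ordinary analysis-plan content, and the analysis plan is not shown. The article also foresees later regression models for the outcomes, and these do not exclude acceptability. All of this stands, and it limits the seriousness of the point. What it does not remove is a main hypothesis of equality paired with a method that cannot support it.

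A reader might infer several stronger things that the documents do not support:

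- *That any result will be reported as equality, or that nothing could count against the hypothesis.* There is no such decision rule, and clearly low or divergent rates would count against it.
- *That equal acceptability is needed to attribute differences in adoption, fidelity or penetration to the training model.* The article does not say so. Attribution rests on randomization by county. Table 2 collects the acceptability form at 6, 12 and 24 months, after training has begun, so an effect of training on how clinicians view PCIT belongs to the training effect.
- *That the plan carries a 30 to 45% risk of missing a 0.5-SD difference.* That is the type II error of a pairwise superiority test with 50 per arm (ICC 0 to 0.2). The plan does not run that test, and running it would not cure the problem.
- *That no interval will ever be reported.* The article is silent on this. Only the absence of a formal test is fixed in print.

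The precision figures also have limits. Wave 1 used two of the three conditions, so arms may be unequal. Table 2 offers other acceptability sources, including the Usage Rating Profile and a family-specific treatment summary, and repeated timepoints, which could change the effective numbers.

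**Conclusion.** The point holds as a minor correction. The article states an equality hypothesis as one of Aim 2's main hypotheses and commits to judging it from rates without a formal test, and similar-looking rates cannot support equality. With about 50 clinician and supervisor respondents per arm, the 95% half-width for a pairwise difference is about 14 to 17 points at rates near 85%, or 0.39 to 0.46 SD. Those figures rest on the assumed equal arms, rate and clinic ICC of 0 to 0.2. The mismatch between hypothesis and method does not depend on them. No other Aim 2 conclusion, and no analysis under Aims 1 or 3, depends on this hypothesis.

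**What to change.** Replace the sentence that rules out a formal test with a commitment to report each arm's rate and the three pairwise differences, with 95% confidence intervals that account for clustering by clinic and county. Reword the hypothesis as descriptive: acceptability and appropriateness are expected to be high and similar. Add that equality will be claimed only if all the intervals lie inside a margin that the sponsor has justified and fixed before analysis. Otherwise the report should say that equality was not shown. A non-significant difference test should not be used in its place.

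The cost is two or three sentences and no new data. The downside is that equality will very probably not be demonstrable at this sample size. A 0.5-SD margin, used here only as an illustration and with no source in the article, would be met in about 1 to 15% of trials even with identical arms. The sponsor should expect to report estimates and intervals rather than a finding of equality.

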### Training conditions

The experimental manipulation in this study was within the Training Design of the Training Transfer Conceptual Model [71]. Table 1 highlights key similarities and differences across groups. Trainers were balanced across conditions. Consistent across each training condition was treatment content (i.e., treatment manual, coding manual, and workbook) and consultation with a trainer.

**Table 1 Tab1:** Condition comparison on key design features

Feature	LC	CM	DE
Primary level targeted	Multiple (senior leader, supervisor, clinician)	Clinician	Clinician
Unique features	1. Addressing multiple organizational levels within the organization that might impact implementation,	1. A “top-down,” hierarchical training approach (EBT expert to a community supervisor to trainees within the community clinician’s organization),	1. Broad public health impact,
	2. Organizing “core teams” (i.e., workgroups) within each organization,	2. Strong and specific focus on two trainees who are advanced clinicians, and	2. Easy access to interactive training program online
	3. Emphasizing cross-site sharing among teams,	3. Extensive use of in vivo skill modeling, direct practice, observation and feedback within the clinic setting.	3. Revieing materials is self-paced, independent, and can be repeated
	4. Utilizing a quality improvement process, which focuses on measuring and monitoring incremental improvements		
Ultimate goal	Create a learning organization	Focus on fidelity	Make training accessible
Trainers—number	3 + admin support	2	1
Trainers—expertise	PCIT, Program Development	PCIT	PCIT
Trainees—number per site and role within organization	2–5 members comprise a “core team.” Minimally include clinicians and supervisors.	2 senior clinicians who also treat families	Unlimited
Training group size (approx)	20 participants from 6 agencies	12 participants from 6 agencies	Unlimited
Training components/ structure	Pre-work phase	5-day initial training;	Web-based training + materials
	3 2-day Learning Sessions	2-day training 6 months after the initial training	
	Action periods between learning sessions		
Time in workshop training	6 days	7 days	None
Consultation (group)	2 h per month	2 h per month	2 h per month
Time frame	12 months	12 months	12 months
Training site	Offsite	Offsite	On-site
Videotape review and feedback	Minimum four tapes per trainee by within agency supervisor	Minimum four tapes per trainee by PCIT expert	None

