#### Cascading model

Consistent with the protocol recommended by the PCIT International Training Committee [85], this condition consisted of 40 hours of initial face-to-face contact with a PCIT trainer, an advanced live training (16 hours ) with real cases 6 months after the initial training, and bi-weekly contact with a trainer conducted over 12 months. After the end of the 12-month intensive training, trainees participated in 6 months of ongoing consultation and training, to begin training others within their organization. Each CM training group included 8 to 12 participants (two clinicians from each organization). Components that make CM unique include the following: (1) a “top-down,” hierarchical training approach; (2) strong and specific focus on two advanced clinicians; (3) extensive use of in vivo skill modeling, direct practice, observation, and feedback within the clinic setting; and (4) capacity for clinicians to return to organization as “in-house” or “within-organization” trainers to replicate clinical training with other clinicians within the organization. CM also focuses on trainers reviewing clinicians' videetaped sessions and providing them with feedback on treatment fidelity and competence. The clinicians trained by “in-house” trainers are also included in the study so that we can understand the impact of a cascading training.

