	Treatment Summary Report [106]	15-item questionnaire to assess nature and outcome of treatment services for a particular family (e.g., service length, barriers, disposition) to provide acceptability data for a specific family	Ongoing as families discharge from treatment	Supervisors	Clinician report and chart review
				Clinicians report on child and family behavior	
Fidelity					
	PCIT Session Fidelity Checklist [107]	Detailed checklists of components of each PCIT session to measure fidelity	Ongoing through video review	Completed by the trainer on clinicians	Behavior observation/ video review
	Use of Treatment Practices [108]	15-item clinician self-report of completion of specific treatment tasks with an individual family	Ongoing as families discharge from treatment	Supervisors	Self-report
				Clinicians	
Cost					
	Chief Financial Officer Survey (updated version of a survey created by Olmstead et al. [109])	Provides information necessary to complete the cost analysis (e.g., program overhead and fringe rates, annual expenditures	Baseline	Administrators	Self-report
Adoption	Time-tracking phone app	Provides time estimates of trainer activity by condition	Ongoing	Trainers	Self-report
	Evidence-Based Practice Survey [110]	List of evidence-based practices respondent has implemented in the last year	Baseline	Administrators	Self-report
			12 months	Supervisors	
			24 months	Clinicians	
Penetration					
	PCIT Learning Experience Feedback Form	Report of consumer levels (e.g., the number of consumers who receive PCIT divided by the number of consumers who were eligible to receive PCIT and did not receive it	6 months	Administrators	Self-report
			12 months		
			24 months		
Sustainability					
	Evidence-based Practice Sustainability Telephone Interview	Survey of current PCIT delivery, penetration, practice adaption, and barriers to sustaining PCIT practice within the organization	24 months	Administrators	Self-report
Family and child outcomes					
Family characteristics					
	Demographic Information	Measure to gather information including age, race, gender, family constellation, living arrangement, school placement, and socio-economic status.	Baseline	Families	Self-report
Child focused			s		
	Eyberg Child Behavior Inventory (ECBI) [111]	36-item parent report of child conduct problems	Baseline	Families	Self-report
			3 months		
			6 months		
			12 months		

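### The ANOVA of cost per clinician treats trainer cost as replicated across clinicians, but that cost is shared by whole training groups and the stated nesting has no level for it

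*Protocol article*

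**What the plan says.** Aim 2 gives cost a directional hypothesis, "we hypothesize that implementation costs will be lowest for the DE and highest for LC", and names a test for it: "We will compare the costs per clinician for the various treatments using ANOVA comparing the three once again". In the same paragraph, acceptability and appropriateness are explicitly exempted from formal testing; cost is not.

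Table 2 lists two cost instruments. One is a Chief Financial Officer survey, answered by administrators at baseline, on overhead, fringe rates and annual spending. The other is a time-tracking app used by trainers, described as follows: "Provides time estimates of trainer activity by condition". As described, neither measures the cost of an individual clinician.

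Table 1 shows how trainer effort is used. LC has "3 + admin support", CM has two trainers and DE one. The LC training group is about "20 participants from 6 agencies" and the CM group about 12 from 6 agencies (8 to 12 in the Cascading model section). Consultation is given in groups, two hours a month, in all three conditions.

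Proposed statistical analyses promises that the ANOVA will respect the nested design. The Nesting section then defines that design as clinicians within clinics and dyads within clinicians.

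**The concern.** A cost that is incurred once for a group and divided by headcount gives every clinician in the group the same value. Entering that value once per clinician adds rows but no information. The within-condition variance then reflects only the other cost components, and the F test counts far more independent observations than exist.

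At stake is one of the four main implementation hypotheses. The Background presents cost as one of the dimensions on which the three models trade off. A p-value or interval for cost that is much too sharp would make that trade-off look better established than it is.

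**Working it through.** The plan gives no sample size, alpha or variance for the cost comparison, so there is no figure of its own to reproduce.

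**1. Independent units.**
- Randomization section: two conditions ran in wave 1 and three in each of waves 2, 3 and 4. Assuming one training group per condition per wave, there are 2 + 3 × 3 = 11 groups.
- Trial status: 100 clinicians in 50 clinics, about 2 per clinic.
- Error degrees of freedom for three conditions: clinicians 100 − 3 = 97; clinics 50 − 3 = 47; training groups 11 − 3 = 8; one total per condition 3 − 3 = 0.

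**2. Does trainer cost per head vary between groups?** The article's own figures suggest that it can. If both CM trainers attend all 7 workshop days (an assumption), a CM group uses 2 × 7 = 14 trainer-days. That is 14/12 = 1.17 per participant in a group of 12 and 14/8 = 1.75 in a group of 8. The value is the same for everyone in a group and differs between groups of the same condition.

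**3. Why the stated nesting is not enough.** Let g be the training-group share of cost variance and c the clinic share.
- Clinicians: about 100/11 = 9.1 per group. The variance of a condition mean is inflated by about 1 + (9.1 − 1)g + (2 − 1)c. At g = 0.05, c = 0.1 this is 1 + 0.405 + 0.1 = 1.5. At g = 0.9, c = 0.1 it is 1 + 7.29 + 0.1 = 8.4.
- Clinic means: about 50/11 = 4.55 clinics per group. The correlation between clinic means within a group is g / [g + c + (1 − g − c)/2]. At g = 0.05, c = 0.1 this is 0.05/0.575 = 0.087, and the inflation is 1 + 3.55 × 0.087 = 1.3. At g = 0.9, c = 0.1 the correlation is 0.9, and the inflation is 1 + 3.55 × 0.9 = 4.2.

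A clinic term therefore reduces the problem but does not remove it.

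**4. Simulation.** 10,000 runs, nominal alpha 0.05 (assumed), no true difference in mean cost, 100 clinicians, 50 clinics, 11 groups. Clinics per wave (5, 18, 13, 14) are from the Randomization section. Their split across conditions within a wave is assumed, as are all variance shares. Entries are rejection rates of a one-way F test.

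| Group share g | Clinic share c | Clinicians | Clinic means | Training-group means |
|---|---|---|---|---|
| 0 | 0 | 4.8% | 5.0% | 4.5% |
| 0.05 | 0.1 | 14% | 11% | 4.7% |
| 0.1 | 0.1 | 23% | 17% | 4.6% |
| 0.3 | 0.2 | 49% | 34% | 5.2% |
| 0.5 | 0.3 | 63% | 43% | 4.9% |
| 0.7 | 0.3 | 72% | 51% | 5.0% |
| 0.9 | 0.1 | 77% | 59% | 4.7% |

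**5. Trainer cost held only by condition.** The simulation does not cover this case. The component then has three values, no within-condition spread and 0 error degrees of freedom, so no F test of it is possible.

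**The case against.** The best defence is that cost per clinician may be a scale and not the unit of analysis: clinic or group cost divided by clinicians trained is also a cost per clinician. The article does not say how the figure is built, a health economist will support the work, and a journal article need not give costing detail. The time log is described in one line and runs continuously, so its entries may already be separable by wave. The reference back to Aim 1 and the Nesting section rule out a test that ignores clinics.

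Much of this stands. The clinic-means column is the fairer reading of the plan, and the clinician column is the worst case. But the defence does not reach the main point: neither the cost paragraph nor the nesting statement contains a training-group or wave level, and clinic nesting still leaves 11% to 59%.

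A reader might infer that the whole cost variable is copies of one number. The documents do not support that. Overhead and fringe rates vary by clinic, a PCIT expert in CM reviews at least four tapes per trainee, and the DE course is self-paced with no workshop and no fixed group size. Nor do they establish that trainer time is the main cost difference; that is only an inference from the trainer counts in Table 1.

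It is also fair to say that equal cost is an artificial null when the conditions are resourced differently by design. The simulated rates show how far the error term is off; they do not show that the hypothesised ordering is false.

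**Conclusion.** The concern holds for the shared part of cost. The trainer component has at most about 11 independent values, or three if kept by condition, and the stated analysis has no level that recognises this. An F test on clinicians or clinics would understate the error, and its p-value and intervals could not be relied on.

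The direction follows from the design, provided that shared cost per head varies between groups of the same condition. The size is unknown, because the documents give no variance shares. The ranges of 14% to 77% and 11% to 59% rest on assumed group shares of 0.05 to 0.9, one training group per condition per wave, and an assumed split of clinics. They should not be quoted as the trial's error rate.

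The consequence is confined to the cost conclusion in Aim 2, an aim worded as exploratory. Training and client outcomes are untouched. It should be corrected, but it does not threaten the trial's other conclusions.

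**What to change.** - State, for each cost component, the unit at which it is measured: condition, training group, clinic or clinician.
- Tag trainer time by training group (condition by wave). The log is ongoing, and dated past entries, if kept, may allow this retrospectively. For DE, which has no fixed group, define the unit as the clinicians trained in that condition in that wave.
- Compute cost per clinician as total group cost divided by clinicians trained, and compare conditions on the training-group means (F on 2 and 8 degrees of freedom). Bootstrapping groups is not a good substitute, because three or four groups per condition are too few for it to be reliable.
- If trainer cost can be recovered only as a total per condition, drop the F test for cost. Report cost per clinician descriptively, with a sensitivity range on unit costs.

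The price is one extra field in the time log and wider intervals. The wider intervals reflect the number of groups actually trained.
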